**Methods/design:**

Three hundred and eighty patients attending routine review at Plymouth Hospitals NHS Trust will be randomised to either enrol immediately into a patient-initiated review system (direct access group), or to be seen regularly by a clinician at the hospital (regular clinician-initiated group). Patients (or their general practitioner) in the direct access group can arrange a review by calling a rheumatology nurse-led advice line that enables telephone delivered clinical advice, or where appropriate, an appointment with a rheumatologist within 10 working days. Patients in the regular clinician-initiated group will attend their planned appointments at regular intervals during the intervening period of 12 months. The primary outcome of interest is patient satisfaction; secondary outcomes include service use, waiting times and clinical measures. Semi-structured, in-depth interviews will be conducted with a subset of patients and staff with the aim of identifying facilitators/barriers in implementing patient-initiated clinics.

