### Direct access group

After randomisation, people in the DA group will be provided with an initial information sheet explaining the system, and will be offered a choice of dates to attend a DA patient education session over the following weeks. The education sessions will comprise small groups of eight people with RA led by a rheumatology specialist nurse, and will focus on issues such as the operation of the DA system, what patients can expect from the system, when and how to call the advice line, when and how to ask for appointments, and any other queries regarding the system [2]. These patients will not be offered routine clinical review, and their GP will be informed about this and sent a short summary of managing common problems experienced by people with established RA. Patients or their GP can arrange prompt clinical advice and a review in clinic where required by calling a rheumatology nurse-led advice line where appointments can be accessed with a maximum delay of ten working days. The education session was piloted on fifty patients and following the feedback from the pilot session, changes were made before delivering it to the patients who are randomised. Any patients declining entry to the DA system will continue to have their care delivered through the traditional review system.

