### Secondary outcome measures

#### Service use

Number of visits to the rheumatology consultant, rheumatology specialist nurse, physiotherapist and occupational therapist will be recorded over the period of 12 months. In a random sample of 50 patients (25 from each group), the cost of the total number of visits to hospital rheumatologists, visits to GPs and allied health professionals for problems related to arthritis and the associated travel costs will be calculated using NHS trust figures and published unit cost data [4].

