## Discussion

The implementation of the DA system in Plymouth will move the service provision from a traditional clinician-driven review system to a more flexible patient-driven system where patients can request help according to their needs. Our evaluation will provide routinely collected data enabling an assessment of the impact of implementing this type of service change in the National Health Service. In addition, the qualitative analysis will offer insights into the reasons why such a service implementation might be successful, and how both health staff and patients perceive both the benefits and drawbacks of such a change.

In the current evaluation we will be able to compare the changes in local services and inform local patients, commissioners and providers about the changes in rheumatology service provision. In the context of a previous RCT, the DA system was established as being more cost-effective, providing greater satisfaction to patients, GPs and rheumatologists, and reduced the delay in follow-up appointments compared with the traditional review system [6]. However RCTs cannot give evidence of how such a service change impacts on the delivery of healthcare in a routine setting. Our expectation is that this implementation of a patient-initiated system of care will reduce unnecessary appointments and costs, be more responsive to patients when they need rapid help, and through these processes empower patients to improve their own self-care. In the current financial climate it will be informative to see if these expectations are realised.

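### The cost outcome leaves out advice-line calls and education sessions, the two inputs through which direct access is delivered, so these items tilt the cost comparison towards direct access by an unknown amount

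*Protocol article*

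**What the plan says.** Two lists appear in the Protocol article under Secondary outcome measures, Service use. The first defines what is counted: "Number of visits to the rheumatology consultant, rheumatology specialist nurse, physiotherapist and occupational therapist will be recorded over the period of 12 months". The second, for 50 randomly sampled patients (25 per group), defines what is costed: "the cost of the total number of visits to hospital rheumatologists, visits to GPs and allied health professionals for problems related to arthritis", together with travel. Neither list mentions the advice line or the education session.

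Both are central to DA elsewhere in the article. Under Direct access group: "Patients or their GP can arrange prompt clinical advice and a review in clinic where required by calling a rheumatology nurse-led advice line". The Abstract, Methods/design, describes DA patients or their GP "calling a rheumatology nurse-led advice line that enables telephone delivered clinical advice, or where appropriate, an appointment with a rheumatologist within 10 working days", so a call can be the whole clinical contact. On education, Direct access group says: "The education sessions will comprise small groups of eight people with RA led by a rheumatology specialist nurse". Implementation process makes this education precede enrolment. Regular clinician initiated group has RC patients move to DA only once the 12 months are over.

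Waiting times uses the call date for one purpose, the interval from call to appointment, and in the DA group only. The Discussion expects that the new system "will reduce unnecessary appointments and costs".

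**The concern.** DA works by removing scheduled visits and putting a telephone line and a preparatory session in their place. The visits removed are in the cost list; the two things that replace them are not. A visit turned into a nurse call is therefore recorded as one visit saved at no cost. Nurse time on the line, nurse time in the sessions and travel to the sessions all drop out.

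At stake is the efficiency conclusion. The Discussion says the evaluation will inform patients, commissioners and providers, and anticipates lower costs. A comparison that leaves out the new service's own running and set-up inputs cannot properly support that conclusion. The primary outcome, patient satisfaction, is not affected.

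**Working it through.** **1. What each resource enters, as written**

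| Resource | Visit count | Cost list | Other quantitative outcome |
|---|---|---|---|
| Consultant or rheumatologist visit | yes | yes | – |
| Specialist-nurse visit | yes | not named | – |
| Physiotherapist or occupational therapist visit | yes | yes, as allied health professionals | – |
| GP visit for arthritis | no | yes | – |
| Call leading to an appointment | no | no | dates the wait (DA only) |
| Call settled by telephone | no | no | none |
| Education session | not stated | not named | none |

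**2. The plan's own figure**

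Inputs from Sample size and statistical analysis: 2.5 (RC) v 2.0 (DA) consultations per year, 5% significance, 90% power, 190 per group. I read consultations as visits. Treating the counts as Poisson and the test as two-sided:

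n = (1.960 + 1.282)² × (2.5 + 2.0) / 0.5² = 189.1, rounded up to 190.

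The stated size reproduces and is not in dispute. The quantity needed here is the planned saving, 2.5 − 2.0 = 0.5 visits per patient-year, or 20%.

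**3. How many extra calls offset that saving**

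The documents give no call volumes and no unit costs, so the weights below are assumptions. In units of one visit, let e be the cost of education per DA patient, k the cost of one call, and c the DA calls per patient-year in excess of RC calls. The first-year saving is 0.5 − e − k·c, which reaches zero at

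c = (0.5 − e) / k.

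Take e = 1/8 = 0.125 (a whole session costs as much as one visit, shared by eight patients, travel ignored) and k from 0.2 to 0.6.

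| k (call as share of a visit) | c without education (0.5/k) | c with education (0.375/k) |
|---|---|---|
| 0.2 | 2.5 | 1.875 |
| 0.4 | 1.25 | 0.94 |
| 0.6 | 0.83 | 0.625 |

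With education included, about 1.9 down to 0.63 extra calls per patient-year offset the planned saving. A session costing more than one visit, or an allowance for travel to it, would lower these figures.

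**4. Direction, item by item**

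- Advice-line calls: DA has no routine review and reaches care through the line, so leaving calls out favours DA to the extent that DA patients call more than RC patients.
- Education session: it falls on DA in the comparison year and on RC only at or after its end, so leaving it out favours DA.
- Specialist-nurse visits: Background describes traditional review as led by a rheumatologist or a specialist nurse, and Regular clinician initiated group has the nurse contact people in both groups who have not been seen. Both arms may use these visits, so the direction is uncertain.

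**The case against.** The case on the other side has several parts.

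- *The visit count is correct for what it measures.* This stands. The Discussion speaks of fewer appointments and the sample size rests on consultations; a 20% fall in visits would be a true result even if calls rose. A reader might infer that the plan makes DA look less used by construction. The documents do not support that: the count is valid for appointments and merely falls short of total workload.
- *Not every omission favours DA.* This stands. A reader might take all the uncosted items to belong to DA. Specialist-nurse visits may be part of RC care, and leaving them out could understate RC cost. The net direction over all omissions is therefore not fixed; the tilt claimed here is for calls and education only.
- *RC patients may also use the line.* This stands as an unknown. The article does not say. If they do, the tilt from calls shrinks; that from education remains.
- *Education may be logged as a nurse visit.* Possibly, in the count, since a specialist nurse leads it. The text does not say so, and the cost list does not name nurse visits. Allied health professionals might be meant to include nurses, but the wording would still cover visits, not calls.
- *Half a call per patient-year does not wipe out the saving.* This stands. A reader might reason that 2.0 visits plus 0.5 calls equals 2.5 contacts, but that treats a call as a visit. On the weights above, 0.5 calls plus education cost between 0.125 + 0.5 × 0.2 = 0.225 and 0.125 + 0.5 × 0.6 = 0.425 visits, less than the 0.5 saved.
- *An article condenses a fuller document.* This carries little weight. The article itemises what is counted and costed, down to travel, and the point concerns the items as listed.

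**Conclusion.** The concern holds for the cost outcome. As written, it omits advice-line calls and education sessions, and calls settled by telephone are measured nowhere in the stated quantitative outcomes. These two omissions tilt the DA-versus-RC cost comparison towards DA. The unnamed specialist-nurse visits are a separate mismatch between the two lists, of uncertain direction.

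The size cannot be fixed from the documents. The offset of about 1.9 to 0.63 extra DA calls per patient-year rests on assumed weights, on the planned 0.5-visit saving being realised, and on charging the whole one-off session to the first year. It shows that an ordinary volume of calls could matter; it does not predict that it will. DA may still be cheaper after full costing. Because the outcome is secondary and confined to 50 patients, this is a point that should be corrected but does not threaten the trial's primary result.

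**What to change.** 1. Log every advice-line call, from patient or GP, in both arms, including calls settled by telephone. State whether RC patients have access to the line.
2. Report visits and calls side by side by arm, keeping the visit count as the measure of appointments.
3. Add to the cost analysis advice-line calls, specialist-nurse visits and, for DA, the education session, valued per patient at 1/8 of the nurse's session time plus travel. Show the result with and without this one-off item, so that set-up and recurrent cost can be told apart.
4. State whether attendance at education counts as a specialist-nurse visit, so that it is neither lost nor counted twice.

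The cost is modest. The waiting-time outcome already needs dates for DA calls that lead to an appointment, but calls settled by telephone and any RC calls would be new recording. The other consequence is a cost figure less favourable to DA on these two items.

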#### Waiting times

As the RC group will attend the clinician-initiated outpatient clinic at regular intervals; service availability upon request will be measured for the DA group only. Waiting time will be assessed by calculating the number of days from the advice line call to the medical appointment.

Semi-structured, in-depth interviews will be carried out with a subset of patients from both groups as well as with the health professionals and administrators involved in providing the service. Interviews will particularly focus on assessing barriers and facilitators of providing a patient-initiated service, reasons for implementation success/failure, psychological benefits/drawbacks and effects on wider life impacts, and perceived or real changes in the interaction between patients and the rheumatology team delivering their medical care. All the interviews will be recorded and later transcribed. Once all the transcripts have been analysed, a matrix will be designed which will enable the emergence of major themes and create an understanding of the individual and group coding. The interviews will add depth to the analysis of quantitative data and will be supplemented through the observation of a sample of patient education sessions given by a rheumatology specialist nurse. The observation of these sessions will allow us to gather first-hand information about the social processes between the specialist rheumatology nurse and patients in an educational context. This will help inform the semi-structured interviews as the qualitative researcher will have first-hand knowledge of how patients were educated about the new appointment system and what were their early thoughts about such process change.

### Sample size and statistical analysis

The assumptions underlying the sample size calculation are derived from a published RCT [6]. In order to detect a decrease in the number of consultations from 2.5 per year in the RC group to 2 per year in the DA group at the 5% significance level with 90% power to detect this difference, we calculated that the current evaluation will require 190 subjects in each group followed up for a period of 12 months. Changes in other outcome measures between the two groups will be compared using simple tests of association such as chi-squared (*χ*^2^) test and Student’s *t*-test (depending on data properties). The qualitative data analysis technique described by Miles and Huberman [15] will be used to analyse the interview data. This means affixing codes to a set of field notes drawn from data collection and sorting through the material to identify relationships between themes. All interview recordings will be transcribed and checked for accuracy. The researcher will listen to the interview recordings and make comments on the transcript and read and re-read them to identify relevant codes. Once all transcripts have been analysed in this way a matrix will be designed which will enable the emergence of major themes and create an understanding of the individual and group coding. Computer aided software such as NVivo (a qualitative data analysis tool that helps to organise and analyse unstructured, i.e. non-numerical data) will be used to interrogate the data at different levels.

## Discussion

The implementation of the DA system in Plymouth will move the service provision from a traditional clinician-driven review system to a more flexible patient-driven system where patients can request help according to their needs. Our evaluation will provide routinely collected data enabling an assessment of the impact of implementing this type of service change in the National Health Service. In addition, the qualitative analysis will offer insights into the reasons why such a service implementation might be successful, and how both health staff and patients perceive both the benefits and drawbacks of such a change.

In the current evaluation we will be able to compare the changes in local services and inform local patients, commissioners and providers about the changes in rheumatology service provision. In the context of a previous RCT, the DA system was established as being more cost-effective, providing greater satisfaction to patients, GPs and rheumatologists, and reduced the delay in follow-up appointments compared with the traditional review system [6]. However RCTs cannot give evidence of how such a service change impacts on the delivery of healthcare in a routine setting. Our expectation is that this implementation of a patient-initiated system of care will reduce unnecessary appointments and costs, be more responsive to patients when they need rapid help, and through these processes empower patients to improve their own self-care. In the current financial climate it will be informative to see if these expectations are realised.

## Ethical approval

After advice from the National Research Ethics Service South-West (Bristol), UK, the quantitative and qualitative evaluations planned for this process do not require full, NHS ethical approval as is it an evaluation of a change in service. However, all interview respondents (both patients and professionals) will be volunteers and will all be provided with a detailed information sheet which describes the nature of the study. Written, informed consent will then be gained using a standardised consent form. Confidentiality will be emphasised at the outset and interview transcripts will be anonymised.
